**Side effects**							

#### Adverse events

Adverse events like symptoms or diseases occurring during the trial will be recorded (Table 2) and assessed at each session of intervention. There may be adverse events of abnormal gastrointestinal reactions, allergic reactions, dizziness, burns, and other medical conditions. The relevance and severity of the adverse events will be assessed. Whether the participant could continue the treatment or not will be decided according to the assessments. Those who suffer harm as a result of the treatment will be compensated in accordance with relevant regulations.

#### Follow-up

To evaluate the incidence of postherpetic neuralgia symptom, a follow-up call is designed and recorded 6 months later posted after the end of the 1-week treatment. (Table 2).

### Outcomes

#### Primary outcome

The primary outcome has been the changes in pain intensity pre- and post-treatment (VAS 0–100 mm, where 0 = *painless* and 100 = *maximum imaginable pain*).

#### Secondary outcomes

First of all, pre- and post-treatment periods, the plasma of the participants is carefully collected and centrifuged and stored in a − 80 °C refrigerator. It is then the substance P and ®-Ep in serum can be detected by an enzyme-linked immunosorbent assay. Quantitative scoring methods have been further applied to evaluate the symptoms and physical signs before and after treatment, including pain intensity, local itching, burning sensation, rash color, numbers of blisters, clusters, ulcers, fever, local lymphadenopathy, and rash area (Table 2).

### Data management and monitoring

The study will be conducted according to the common guidelines for clinical trials (Helsinki Statement, 2008 Chinese Edition, http://www.chictr.org.cn/index.aspx) and will be jointly audited by the Audit Office, Science and Technology Department and Finance Department of Kunming Medical University. Trial auditing will be twice a year since that is the frequency of meeting with the Trial Steering Group of principal investigators. Data will be uploaded to the ResMan Public Management Platform of the China Clinical Trial Registry for adequate quality and safety control. The registration number is ChiCTR1800015372. Therefore, no Data Safety Monitoring Committee is needed. The principal investigator is responsible for project oversight, will make the final decision to terminate the trial, and will have access to the final trial dataset.

### Confidentiality and dissemination

The personal information of all the participants stored on computers is kept on a secure server and will always be kept confidential. All the documentations of this study will be kept in a locked and secure environment (locked office and cabinets) at the Six Affiliated Hospital of Kunming Medical University. The review will be submitted to a peer-reviewed journal prospectively to spread our findings.

### Statistical methods

#### Sample size estimation

We will compare the difference in efficacy of the three groups. Sample size estimation is based on the method of the book of *Health statistics* [15], with type I error alpha = 0.05 and type II error beta = 0.1, using the bilateral test. According to the literature, the cure rates of famciclovir and for fire needle plus cupping for HZ were 37.8% and 76.4%, respectively. It was speculated that the cure rate of famciclovir plus fire needle plus cupping was 80.0%, which was substituted into the formula:

$$ n=\frac{2\lambda }{{\left(2{\sin}^{-1}\sqrt{p_{\mathrm{max}}}-2{\sin}^{-1}\sqrt{p_{\mathrm{min}}}\right)}^2} $$where *P*_max_ = 0.80 and *P*_min_ = 0.378. The calculated result was a sample size of 32 subjects per group. Therefore, the number of samples required for the three groups was 96. This study required a total of 105 samples adding a 9–10% dropout rate.

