**Discussion:**

The results of this trial aim to provide sufficient evidence on FC treatment over both FG and FCF treatments. It will then give a credible alternative treatment to cut down acute pain and to cure AHZ infection.

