#### Statistical analysis

The purpose of this study is to confirm whether the therapeutic effect of experimental therapy (fire needle cupping) is different from that of reference therapy (famciclovir plus gabapentin and fire needle cupping plus famciclovir). SPSS 20.0 statistical software will be used for data analysis. When the main efficacy indicators of individual subjects are missing, the last observation carried forward will be conducted, and the non-main efficacy indicators will not be carried forward. The mean ± standard deviation is used for statistical description of measurement data, and the frequency (constituent ratio) is used for statistical description of counting data. The baseline characteristics will be recorded as in Table 3. The group *t* test (Bonferroni method) will be used to compare the measurement data between groups. All reported *P* values will be two-tailed with 95% confidence intervals. The value of *P* ≤ 0.05 will be considered statistically significant. PPS analysis and Fas analysis will be performed at the same time. SS analysis is used for safety evaluation.

**Table 3 Tab3:** Baseline characteristics

Characteristics	Value
Age, mean ± SD, year	
Gender, *n* (%)	
Male	
Female	
Onset days, mean ± SD, days	
VAS score, mean ± SD	
Quantitative score, mean ± SD	

Onset days are the time from the patient’s onset of pain or rash to inclusion

Quantitative score is quantitative score of symptoms and signs

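### The sample size and its beta of 0.1 rest on cure rates, so the 90% power does not apply to the primary VAS comparison, whose power is unknown

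*Protocol article*

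**What the plan says.** All references are to the protocol article.

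- **Sample size estimation.** The calculation is made "with type I error alpha = 0.05 and type II error beta = 0.1, using the bilateral test". Its inputs are proportions cured: "According to the literature, the cure rates of famciclovir and for fire needle plus cupping for HZ were 37.8% and 76.4%, respectively". For the combination arm, "It was speculated that the cure rate of famciclovir plus fire needle plus cupping was 80.0" per cent. An arcsine formula is applied to the largest and smallest of these (0.80 and 0.378). "The calculated result was a sample size of 32 subjects per group", so "the number of samples required for the three groups was 96", raised to 105 for dropout.
- **Primary outcome.** "The primary outcome has been the changes in pain intensity pre- and post-treatment", measured on a 0–100 mm VAS. The abstract says the same.
- **Secondary outcomes and Table 2.** These are substance P, beta-endorphin, analgesic need, side effects and ordinal symptom and sign scores. There is also a six-month call for postherpetic neuralgia. No cure outcome or cure threshold appears.
- **Statistical analysis.** For continuous data the test is a t test ("Bonferroni method) will be used to compare the measurement data between groups"). Count data are described by frequency, with no between-group test named. The stated purpose is to find whether fire needle plus cupping (FC) differs from each of the two reference arms, famciclovir plus gabapentin (FG) and FC plus famciclovir (FCF).

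**The concern.** A sample size justification should tell the reader what the primary analysis can detect. Here the only error rates stated for the design relate to a proportion that the article does not list as an outcome, under a test that it does not plan to run. Nothing links a cure rate to millimetres of VAS change.

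What is at stake is the reading of the primary result, above all a null one. If FC and FCF do not differ on VAS, a reader will want to know whether the trial could have shown a difference worth having. The stated beta of 0.1 looks like the answer but cannot give it.

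**Working it through.** **1. Reproduce the plan's figure.** The inputs are in Sample size estimation: alpha 0.05, beta 0.1, Pmax = 0.80, Pmin = 0.378. The article does not print lambda. For a chi-square test with 2 df (three groups) at 90% power, lambda = 12.654.

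- 2·asin(√0.80) = 2.2143 and 2·asin(√0.378) = 1.3243, so the gap is 0.890 and its square 0.792.
- n = 2 × 12.654 / 0.792 = 31.95, rounded up to 32. Three groups give 96.
- 96 × 1.09 = 104.6, rounded up to 105, or 35 per group.

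With the 1-df value (lambda = 10.507) the formula gives 26.5, which does not match. The 90% is thus the power of an omnibus three-group test of proportions cured.

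**2. Set it beside the planned primary analysis.**

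| | Sizing calculation | Primary analysis |
|---|---|---|
| Variable | Cured, yes or no | VAS change, continuous |
| Test | Arcsine, 2 df, omnibus | Pairwise t tests, Bonferroni |
| Effect assumed | 37.8%, 76.4%, 80.0% | None given |
| SD | Not needed | None given |

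**3. What 32 evaluable per arm can detect on VAS.** For a two-sample t test, df = 2 × 32 − 2 = 62 and the noncentrality is d × √(32/2) = 4d, where d is the difference divided by the SD of VAS change. Power is the probability that a noncentral t exceeds the two-sided critical value. Solving for 90%:

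| Alpha per test | Case | d | SD 15 | SD 20 | SD 25 | SD 30 |
|---|---|---|---|---|---|---|
| 0.05 | unadjusted | 0.82 | 12.3 mm | 16.5 mm | 20.6 mm | 24.7 mm |
| 0.05/2 = 0.025 | two contrasts | 0.90 | 13.5 mm | 18.0 mm | 22.5 mm | 27.0 mm |
| 0.05/3 = 0.0167 | three contrasts | 0.94 | 14.1 mm | 18.8 mm | 23.5 mm | 28.2 mm |

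The SDs are assumptions, since the article gives none.

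**4. Power over a range of assumed differences,** 32 per arm, shown as alpha 0.0167 / alpha 0.05:

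| Assumed difference | SD 15 | SD 20 | SD 25 | SD 30 |
|---|---|---|---|---|
| 10 mm | 58% / 75% | 33% / 50% | 20% / 35% | 14% / 26% |
| 15 mm | 93% / 98% | 70% / 84% | 48% / 66% | 33% / 50% |
| 20 mm | >99% / >99% | 93% / 98% | 77% / 88% | 58% / 75% |

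The table falls on both sides of 90%. Which cell applies depends on two inputs that the article does not state.

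**The case against.** **The statistical analysis plan may deal with this.** It could add a cure analysis or a VAS power statement, and the article is a condensed account. That is fair as far as it goes, so the supportable wording is that cure is not defined, listed or analysed in this document, not that it never will be. But the sizing basis is set out here in full, and a later cure analysis would not make it apply to VAS change.

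**The article never claims 90% power for VAS.** True. It gives beta = 0.1 in a paragraph that openly uses cure rates. The defect is that this is the only power statement offered and it is not tied to the primary outcome.

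**Stronger readings that the article does not support.**

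- A reader might infer that the trial is underpowered for VAS. Showing only a 10 mm difference would suggest so, but nothing in the article makes 10 mm the target, and 15–20 mm gives anything from about 33% to over 99% at alpha 0.0167.
- A reader might infer that the sample size is miscalculated. It is not: 32, 96 and 105 all follow from the stated inputs.
- The abstract's discussion says of the results: "It will then give a credible alternative treatment to cut down acute pain and to cure AHZ infection". A reader might infer a prespecified claim with no outcome behind it. This is a loose sentence about aims. Table 2 does score healing signs such as blisters, ulcers and rash area, although it sets no threshold for cure. It is a separate and minor wording point.

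**The mismatch causes no bias.** This also stands. It does not distort the estimate, inflate type I error or alter the conduct of the trial.

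**Conclusion.** The point holds in this form: the stated alpha, beta and n describe a 2-df comparison of cure rates, and the 90% power does not carry over to the Bonferroni t tests on VAS change. Power for the primary analysis is unknown, not shown to be low.

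The mismatch itself needs no assumption, because it is visible from the article's own sections. The detectable differences of 0.82, 0.90 and 0.94 SD assume 32 evaluable patients in each arm, equal variances and a two-sided t test on change. All figures in mm, and all power figures, rest on assumed SDs of 15–30 mm and, for power, assumed differences of 10–20 mm.

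**What to change.** In Sample size estimation:

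1. State that beta = 0.1 refers only to the cure-rate calculation and not to the primary outcome.
2. Add the VAS-change difference detectable with 90% power by the planned Bonferroni t tests at 32 evaluable per arm: 0.90 SD if two contrasts are tested, 0.94 SD if three. Say which number of contrasts applies.
3. Convert that to mm with an SD of VAS change taken from a named source, and set it against a target VAS difference with its justification. This pair of inputs is the real gap; a detectable difference in SD units alone does not fill it.

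Separately, and as a minor edit, limit the abstract's wording about curing the infection to the outcomes that the trial lists.

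The cost is finding a sourced SD and target difference and revising the text. No extra patients and no change to treatment are needed. The downside is that the restated power may prove less favourable than 90%.

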#### Group B

Patients in group B are intervened with famciclovir plus gabapentin (FG). The famciclovir hydrochloride dosage is 0.25 g/time, 3 times a day according to the manufacturer’s (Livzon Pharmaceutical Factory) recommendation. The individual dose of gabapentin is 900–3600 mg per day. According to the manufacturer’s (Jiangsu Hengrui Pharmaceutical Co., Ltd.) recommendation (Table 1), the initial dose of 300 mg per day is gradually increased to 900 mg per day and then increased according to the patient’s needs, and the maximum dose is 3600 mg per day.

**Table 1 Tab1:** Gabapentin scheme

Day time	8:00 a.m.	14:00 p.m.	22:00 p.m.
1	–	–	300 mg
2	300 mg	–	300 mg
3	300 mg	300 mg	300 mg
Increase depending on patient’s needs			
4	300 mg	300 mg	600 mg
5	600 mg	300 mg	600 mg
6	600 mg	600 mg	600 mg
7 (maximum dose)	1200 mg	1200 mg	1200 mg

Table 1 demonstrates the gabapentin intake scheme used to reach the wanted therapeutic dosage.

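### The 90% power and 32 per group are derived from cure rates, so the stated power does not apply to the primary analysis of change in VAS

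*Protocol article*

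**What the plan says.** All references are to the protocol article.

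- **Sample size estimation.** The error rates are set as "with type I error alpha = 0.05 and type II error beta = 0.1, using the bilateral test". The inputs are literature rates: "the cure rates of famciclovir and for fire needle plus cupping for HZ were 37.8% and 76.4%, respectively". For the combination arm the authors speculate that "the cure rate of famciclovir plus fire needle plus cupping was 80.0" per cent. The largest rate (0.80) and the smallest (0.378) go into an arcsine formula, and "The calculated result was a sample size of 32 subjects per group". The three groups then total 96, and "This study required a total of 105 samples adding a 9–10% dropout rate".
- **Primary outcome.** "The primary outcome has been the changes in pain intensity pre- and post-treatment", on a 0–100 mm VAS.
- **Secondary outcomes, Table 2 and Follow-up.** These list substance P, β-endorphin, symptom and sign scores, analgesic demand, side effects and postherpetic neuralgia at 6 months. No cure endpoint appears.
- **Statistical analysis.** For the group t test the text reads "Bonferroni method) will be used to compare the measurement data between groups". Count data are described by frequency and no test is named for them. The stated purpose is to compare fire needle plus cupping (A) with each reference therapy, that is A v B and A v C. Full analysis set and per-protocol analyses are both planned, with last observation carried forward for the main efficacy measure.
- **Group B.** "Patients in group B are intervened with famciclovir plus gabapentin (FG").

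**The concern.** A power statement belongs to one endpoint, one test and one set of assumed effects. Here the endpoint behind the calculation is a cure proportion, while the endpoint to be analysed is a continuous pain change. The calculation compares three proportions through their extremes; the analysis is a set of adjusted pairwise t tests. The lowest rate is cited for famciclovir, whereas the arm it stands for is assigned famciclovir plus gabapentin.

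At stake is how the result will be read. A non-significant A v B or A v C difference on VAS could be taken as coming from a trial with 90% power, although that figure was never worked out for VAS. Nor can a reader tell how large a pain difference the trial is able to detect.

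**Working it through.** **1. Reproducing the plan's figure.**

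Inputs from Sample size estimation: Pmax = 0.80, Pmin = 0.378, alpha 0.05 two-sided, beta 0.1. Formula as printed: n = 2λ / (2·asin√Pmax − 2·asin√Pmin)².

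- 2·asin√0.80 = 2.214 and 2·asin√0.378 = 1.324. The difference is 0.890 and its square 0.792.
- The article does not print λ. As the noncentrality of a chi-square test with 2 degrees of freedom (three groups), λ = 12.654, so n = 2 × 12.654 / 0.792 = 31.95, rounded up to 32.
- With 1 degree of freedom (two groups), λ = 10.507, so n = 26.5, rounded up to 27.

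The printed formula returns 32 only with the 2-degree-of-freedom value. That the calculation is an overall three-group comparison is therefore a back-calculation, not something the article states. The total follows: 3 × 32 = 96, raised to 105, or 35 per group.

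**2. Setting the calculation beside the analysis.**

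| | Sample size section | Primary analysis |
|---|---|---|
| Endpoint | Cure (undefined, not listed) | Change in VAS, mm |
| Test | Three-group comparison of proportions (inferred) | Pairwise t tests, Bonferroni |
| Contrast driving it | Highest v lowest rate, i.e. C v B | A v B and A v C |
| Group B | Rate cited for famciclovir | Famciclovir plus gabapentin |
| VAS difference, SD | None | None |

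**3. What the sample size gives on VAS.**

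For a two-sample t test with n per group, the noncentrality is d·√(n/2) on 2n − 2 degrees of freedom, where d is the true difference divided by the SD. Solving for 90% power, two-sided:

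| n per group | alpha 0.05 (unadjusted) | 0.025 (two contrasts) | 0.0167 (three contrasts) |
|---|---|---|---|
| 32 (evaluable) | 0.82 SD | 0.90 SD | 0.94 SD |
| 35 (all randomised) | 0.79 SD | 0.86 SD | 0.90 SD |

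Check for n = 32, alpha 0.0167: 0.941 × √16 = 3.76, against a critical t of 2.46 on 62 degrees of freedom, gives 90%.

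**4. Conversion to mm.**

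The article gives no SD, so 15, 20 and 25 mm are assumptions chosen to show the range. With 32 per group:

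- 0.90 SD (0.899 unrounded) is 13.5, 18.0 and 22.5 mm.
- 0.94 SD (0.941 unrounded) is 14.1, 18.8 and 23.5 mm.

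**5. Is 32 enough for VAS?**

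For an assumed true difference of 15 mm and 32 per group, power for SDs of 15, 20 and 25 mm is 95%, 76% and 54% at alpha 0.025, and 93%, 70% and 48% at 0.0167. The size could be ample or too small. The article's own figures do not settle which.

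**The case against.** **The article condenses a fuller protocol.** That would excuse silence, but the article prints the formula, inputs and result, and these conflict with its own primary outcome and analysis. No fuller text turns a cure-rate calculation into a VAS power statement.

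**The three-group formula fits the stated aim.** The sample size section speaks of comparing efficacy across three groups, and the Discussion of testing all three treatments. This stands as far as it goes: a formula built on the highest and lowest rates is not odd in itself, and on the plan's cure rates A v B at unadjusted 0.05 has about 90% power. It does not help VAS.

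Four stronger readings are tempting, and the documents do not support them:

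- *The trial is underpowered for VAS.* This cannot be shown without a difference and an SD.
- *Cure-related data are not collected at all.* Table 2 scores pain, blisters, ulcers and rash area, from which a cure measure might be derived. The supported statement is that cure is neither defined nor listed as an outcome.
- *The Bonferroni tests miss 90% even on the plan's cure rates.* The plan applies Bonferroni to measurement data and proposes no such test of proportions, so that shortfall belongs to an analysis nobody has planned.
- *Gabapentin makes group B's cure rate much higher than 37.8%, so power collapses.* Nothing in the article gives a rate for the combination. The Study design section makes gabapentin depend on patient need, while the Group B section sets out a schedule. The cited source is not at hand. What stands is a mismatch between the cited treatment and the assigned one, of unknown size.

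**Conclusion.** The point holds in this form: the 90% power and 32 per group rest on cure rates, and the 90% therefore cannot be attached to the primary comparison of VAS change. The arithmetic is correct; the endpoint and the test are the wrong ones for the claim.

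The size of the gap in power cannot be stated. What can be stated is the standardised difference detectable with 90% power under Bonferroni: 0.90 to 0.94 SD with 32 per group, and 0.86 to 0.90 SD if the full analysis set holds all 35. These figures assume equal SDs and a simple two-sample t test on the change. The mm values also rest on assumed SDs. The lower end of each range counts the two contrasts named in the statistical analysis section, and the upper end counts all three pairs. The article does not say which number of contrasts Bonferroni will use.

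**What to change.** Keep 105 patients and rewrite the power statement:

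1. Remove the cure-based 90% power claim for the primary outcome.
2. State how many contrasts Bonferroni covers, then give the VAS difference detectable with 90% power at that alpha: 0.90 SD (two contrasts) or 0.94 SD (three) with 32 evaluable per group, and 0.86 or 0.90 SD with all 35 in the full analysis set. Do not lead with the unadjusted 0.05 figure.
3. Convert it to mm with a stated and justified SD, and say whether a difference of that size is plausible and clinically relevant.
4. Apply the same statement to A v C as to A v B.
5. If cure is to be kept, define it and list it as a secondary outcome with its own test, and do not present the famciclovir rate as group B's rate without justification.

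The cost is protocol wording, with no added patients. The downside is that the stated detectable effect becomes less favourable than the present 90% claim suggests.

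### The 90% power belongs to an overall three-group comparison that the analysis section does not state; on the plan's own cure rates, FC v FG by Bonferroni pairwise testing has about 79–87%

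*Protocol article*

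**What the plan says.** **Sample size estimation.** The aim is put as a three-group one: "We will compare the difference in efficacy of the three groups". The error rates are "type I error alpha = 0.05 and type II error beta = 0.1, using the bilateral test". The planning rates are "the cure rates of famciclovir and for fire needle plus cupping for HZ were 37.8% and 76.4%, respectively", and for the combination arm: "It was speculated that the cure rate of famciclovir plus fire needle plus cupping was 80.0%, which was substituted into the formula". The arcsine formula printed there takes only the maximum (0.80, FCF) and the minimum (0.378, famciclovir); its constant lambda is not given a value. "The calculated result was a sample size of 32 subjects per group", so 96 in all, raised to 105 for dropout.

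**Statistical analysis.** The purpose is "to confirm whether the therapeutic effect of experimental therapy (fire needle cupping) is different from that of reference therapy", and the reference therapies named there are FG and FCF. The between-group method is a group t test ("Bonferroni method) will be used to compare the measurement data between groups"). The number of Bonferroni contrasts is not given. Count data get a descriptive summary only.

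**Primary outcome.** This is the change in VAS pain score, not a cure rate.

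**The concern.** A power figure describes one test of one contrast. Here the sizing section describes a three-group comparison whose effect size is the gap between FCF and famciclovir. The analysis section describes adjusted pairwise comparisons centred on FC, which is neither the maximum nor the minimum arm.

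Two things then lower the power for FC v FG relative to the stated 90%. Its assumed gap (76.4% v 37.8%) is narrower than the one used, and each pairwise test is run at a divided alpha. A reader would take the type II error of 0.1 to apply to the question the trial says it answers. If FC v FG came out non-significant, the strength of that negative result would be overstated.

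**Working it through.** **Inputs** (all from Sample size estimation unless noted): two-sided alpha 0.05; beta 0.10; rates 0.764 (FC), 0.378 (famciclovir, standing in for FG, for which no rate is given) and 0.80 (FCF, speculated); 32 per group evaluable; 105/3 = 35 per group randomised. Assumption: two Bonferroni contrasts (the two in the purpose sentence) or three (all pairs).

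**1. Reproduce the 32.** On the scale 2·asin(√p) the rates become 2.127 (FC), 1.324 (famciclovir) and 2.214 (FCF).
- Maximum–minimum gap: 2.214 − 1.324 = 0.890; squared, 0.792.
- Lambda is the chi-square noncentrality for 90% power at 0.05: 12.654 on 2 df, 10.507 on 1 df.
- 2 df: n = 2 × 12.654 / 0.792 = 31.95, so 32. This matches.
- 1 df: n = 2 × 10.507 / 0.792 = 26.5, so 27. This does not.

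The 90% is therefore the power of an overall three-group test. It is the least favourable case for that gap, with the third group midway. With all three planning rates put in, overall power at 32 per group is 94.9%. Dropout: 96 × 1.09 = 104.6, so 105.

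**2. Power for FC v FG.** Gap h = 2.127 − 1.324 = 0.803. Power = Φ(h·√(n/2) − z), where z is 1.960 at 0.05, 2.241 at 0.05/2 and 2.394 at 0.05/3.
- n = 32: h·√16 = 3.211.
- n = 35: h·√17.5 = 3.358.

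| Alpha per contrast | n = 32 | n = 35 |
|---|---|---|
| 0.05/3 | Φ(0.817) = 79.3% | Φ(0.964) = 83.2% |
| 0.05/2 | Φ(0.970) = 83.4% | Φ(1.117) = 86.8% |
| 0.05 (undivided) | Φ(1.251) = 89.5% | Φ(1.398) = 91.9% |

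The type II error over the four Bonferroni cells runs from 1 − 0.868 = 0.132 to 1 − 0.793 = 0.207.

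**3. Check by other methods at 0.05/3.** Pooled z gives 78.5% (n = 32) and 82.7% (n = 35). The chi-square test by exact enumeration gives 79.1% and 84.3%. Fisher's exact test is lower, at 70.3% and 78.8%.

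**4. The alternative analysis.** Overall 2-df test at 0.05, then FC v FG at 0.05 only if the overall test is significant; 2,000,000 simulated trials on the arcsine scale at the three planning rates. FC v FG power is 88.2% at n = 32 and 91.0% at n = 35.

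**The case against.** **The 32 is right.** It is, for the test it sizes. A reader might infer a calculation error; the arithmetic does not support that. The fault is that two stated elements do not match.

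**The pairwise figures are themselves powers of a test the plan does not state.** This is the strongest objection, and much of it stands. Bonferroni is planned for a t test on measurement data, cure rate is not among the listed outcomes, and no test is given for count data. The figures carry the only effect sizes in the plan over to the only multiplicity method in the plan. They show what the 90% becomes on its own terms. They do not give the power of the VAS analysis, which cannot be computed because the plan states no VAS difference or standard deviation.

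**No FG rate is given.** Correct: 37.8% is quoted for famciclovir, and group B also receives gabapentin. It is used here as a stand-in, as the plan's own sizing does.

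**An overall test may still be intended.** A condensed article can omit it, the analysis plan is not shown, and the sizing section speaks of comparing three groups. So a reader may not conclude that the trial never runs one, only that the article does not state one. The point does not depend on the omission: a significant overall test would not by itself show that FC differs from FG, and the pairwise tests are stated as Bonferroni-adjusted.

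**The shortfall may be small.** True at one end. The purpose sentence names two contrasts, and last observation carried forward in a full analysis set could keep all 35 per arm; power is then 86.8%. A reader might say that the type II error doubles, but that holds only for three contrasts at 32 per arm (0.207).

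**Conclusion.** The concern holds as a mismatch between the test that was sized and the tests that are stated. The 90% is the power of an overall three-group comparison of cure rates, driven by a speculated FCF rate against a famciclovir rate. For FC v FG, Bonferroni pairwise testing on the same rates gives 79% or 83% power (three or two contrasts) at 32 evaluable per arm, and 83% or 87% at 35. The shortfall is about 3 to 11 percentage points: moderate, but on the contrast that bears most directly on the stated purpose.

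This rests on the plan's cure rates at face value, on famciclovir standing in for FG, on two or three contrasts, and on the arcsine approximation (Fisher's test would be lower). It says nothing about the power of the VAS comparison in either direction.

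**What to change.** Keep 105 patients and do one of the following.

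(a) **Restate the sizing.** In Sample size estimation, say that 32 per group gives 90% power for the overall three-group comparison of cure rates. Add that FC v FG under Bonferroni has about 79–87%, depending on the number of contrasts and on dropout. Label this as a cure-rate figure that does not describe the VAS analysis, and state the number of contrasts. *Cost:* one or two sentences, and a less favourable stated power.

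(b) **Make the analysis match the sizing.** In Statistical analysis, run an overall three-group test at 0.05 and, if it is significant, each pairwise test at 0.05, in place of Bonferroni. With exactly three groups this is a closed procedure: if any two of the pairwise null hypotheses are true, all three groups are equal, so the overall test is the only higher-level test needed. The family-wise error stays at 0.05. On the planning rates FC v FG has about 88% power at 32 per arm and 91% at 35, again for cure rate only. *Cost:* one or two sentences; simultaneous confidence intervals are less simple than under Bonferroni.

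Option (b) is preferable because it recovers most of the stated power with no more patients.
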